### Randomisation

A block randomisation schedule to maintain balance between treatment arms has been prepared by an independent statistician, not directly involved in the analysis of the study results, from the Clinical Epidemiology and Biostatistics Unit (CEBU) at the RCH and supplied to Pharmacy who dispense the study product. Randomisation is stratified by method of infant feeding (breastfed versus formula-fed) and age at the time of study commencement (≤6 weeks versus >6 weeks, due to the natural crying peak occurring at around six weeks of age). Infants on a mixture of both breast- and formula-feeding are allocated to the formula-fed stratum. To minimise potential biases, the study is double-blind whereby treatment allocation is concealed from all study investigators and participants.

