**Primary Outcome**								
Infant crying/fussing time (mins/day)					■		Study diary	A validated measure of infant crying/fussing/sleep/feeding and records these behaviours in 5 minute epochs over 24 hours [65-67]. At baseline parents record in the study diary for 24 hours. At other time-points, the diary is filled in over 48 hours. This is to account for daily variability in infant behaviour whilst taking into account the potential burden to families from filling in the diary for prolonged periods of time.

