### Data analysis

#### Estimation of sample size

We have selected a sample size of 160 to provide 80% power to detect a minimum effect size of 0.5 standard deviations, difference in the mean daily crying time between treatment groups with a significance level of p < 0.05, allowing for a drop out rate of 20%. If the data are substantially skewed, 80% power would be maintained to detect a minimum effect size of 0.525 [63,64]. In Savino’s trial [60], the percentage reduction in median daily crying time at day 28 compared to baseline was 70% for the probiotic and 26% for simethicone, suggesting substantive differences in this outcome are likely. With a much larger sample size (double that of Savino’s trial) in our study, we are confident we would also be able to detect a smaller difference in daily crying time reduction. Our sample size of 160 infants provides 80% power to detect a minimum effect size of 0.85 standard deviations, difference in the mean daily crying time between treatment groups within either the formula-fed or breastfed babies, assuming 40% of infants in the sample are exclusively breastfed.

We will be conducting an intention-to-treat analysis in which participants are compared according to the group to which they were randomly allocated regardless of participants' compliance, crossover to other treatments or withdrawal from the study. This approach preserves the prognostic balance in the study arms achieved by randomisation.

Baseline characteristics and study outcomes will be described for each treatment group using means and standard deviations for normally distributed continuous outcomes, while medians and inter-quartile ranges will be used for continuous outcomes that are skewed. Proportions for categorical data will be given. All primary and secondary outcomes for the intervention versus control groups will be compared with t tests and non-parametric tests for continuous data, and chi squared tests for dichotomous data. The primary outcome is the crying time/24 hours at day 28. We will additionally consider a dichotomised indicator of treatment response defined as a 50% reduction in crying time. Subgroup analyses are intended a priori to examine treatment differences amongst breastfed babies and those who are formula-fed, and amongst infants with a family history of atopy and those without.

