Regression models will be used to estimate treatment effect sizes, odds ratios and 95% confidence interval, adjusting for potential confounding factors identified a priori and measured at baseline. These include infant age (≤6 weeks versus >6 weeks, taking into account the natural course of infant colic symptomatology with the peak of crying at six weeks), mode of birth delivery, maternal smoking, use of antibiotics or probiotics in infants and breastfeeding mothers, maternal diet if breastfeeding, maternal mental health scores, and known causes of crying (e.g. fever, eczema, vaccination, vomiting, and diarrhoea). Random effects regression models will be used for further longitudinal analysis examining trends in crying time within individual babies.

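### The planned comparison of day-28 crying/fussing time gives away precision: neither baseline crying/fussing time nor the feeding stratum is in the analysis

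*Protocol article*

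**What the plan says.** The primary outcome is crying/fussing time per 24 hours at day 28, a follow-up value and not a change from baseline. On the comparison, the Data analysis section says: "All primary and secondary outcomes for the intervention versus control groups will be compared with t tests and non-parametric tests for continuous data". No covariate enters that comparison.

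The same section then describes regression models that adjust for factors chosen in advance and measured at baseline. The listed factors are infant age group, recognised triggers of crying such as fever or vaccination, and these: "mode of birth delivery, maternal smoking, use of antibiotics or probiotics in infants and breastfeeding mothers, maternal diet if breastfeeding, maternal mental health scores". The list is introduced by a word that leaves it open.

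Two variables are not on it:

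- **Baseline crying/fussing time.** Table 1 shows that it is collected: "At baseline parents record in the study diary for 24 hours".
- **Feeding method.** The Randomisation section says: "Randomisation is stratified by method of infant feeding (breastfed versus formula-fed") and also by age at study commencement, at or below versus above 6 weeks. Age is on the adjustment list; feeding is not, although the Data analysis section makes it a planned subgroup factor.

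**The concern.** The value of an outcome at baseline is usually the first covariate to consider for its value at follow-up. Here the list names delivery mode and maternal smoking but not the infant's own crying at entry. An unadjusted test leaves in the error term all the between-infant variation that baseline crying could explain.

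Feeding raises a separate, smaller matter. Stratified randomisation forces balance on the stratifying factors. If such a factor is prognostic and the analysis ignores it, the standard error is larger than the design warrants, so the test is conservative. Including one stratifier and not the other has no evident reason. Maternal diet if breastfeeding is at most a partial stand-in for feeding method.

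What is at stake is the width of the confidence interval and the power for the main question, from infants and diaries the trial already has.

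**Working it through.** **Inputs from the protocol article (Data analysis, Estimation of sample size).** Total 160; "80% power to detect a minimum effect size of 0.5 standard deviations"; "with a significance level of p < 0.05", taken as two-sided because that reproduces the total; 20% drop-out; 40% of infants exclusively breastfed. Mixed-fed infants go to the formula stratum, so the strata split 40/60. Equal allocation is assumed.

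**Input not in the document.** The correlation r between baseline and day-28 crying/fussing time. I take 0.1 to 0.5.

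**Step 1: reproduce the plan's figure.** A two-sample t test at 0.5 SD, two-sided 5%, 80% power needs 63.8, so 64, per arm. That is 128 analysed, and 128 / 0.80 = 160, as stated. The normal approximation gives 63 per arm, and 126 / 0.80 = 157.5, so 158. Power with 64 per arm is 80.1% from the noncentral t. The sample size therefore rests on the unadjusted comparison and is correct for it.

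**Step 2: adjust for baseline.** The residual SD becomes √(1 − r²) of the original, so:

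- the standardised effect becomes 0.5 / √(1 − r²);
- the detectable difference becomes about 0.5 × √(1 − r²);
- 128 infants are worth 128 / (1 − r²) under the unadjusted test.

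The one lost degree of freedom is ignored.

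| r | Variance removed (r²) | Power at 0.5 SD, 64 per arm | Detectable difference (SD) | Equivalent unadjusted total analysed |
|---|---|---|---|---|
| none | 0% | 80.1% | 0.50 | 128 |
| 0.1 | 1% | 80.5% | 0.497 | 129 |
| 0.2 | 4% | 81.7% | 0.490 | 133 |
| 0.3 | 9% | 83.7% | 0.477 | 141 |
| 0.4 | 16% | 86.5% | 0.458 | 152 |
| 0.5 | 25% | 90.0% | 0.433 | 171 |

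**Step 3: where r might lie.** Three features of the trial push it down: entry requires at least 3 hours of crying or fussing a day (Inclusion criteria), which narrows the baseline range; the baseline diary covers a single 24 hours (Table 1); and colic remits naturally beyond about 12 weeks of age (Background). To illustrate the first, suppose a normal model in which only infants above the mean enter. The baseline variance falls to 1 − 2/π = 0.363 of its unselected value, and r becomes r√0.363 / √(1 − r² + 0.363r²). An unselected r of 0.3 then becomes 0.19, and 0.5 becomes 0.33. Entry is by caregiver report, so the real narrowing may be weaker.

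**Step 4: add the feeding stratum alone.** If the strata differ by g SD, the share of variance explained is 0.4 × 0.6 × g² = 0.24g².

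| g (SD) | Variance explained | Power | Gain over 80.1% |
|---|---|---|---|
| 0.2 | 1.0% | 80.5% | 0.4 points |
| 0.3 | 2.2% | 81.0% | about 0.9 points |
| 0.5 | 6.0% | 82.5% | 2.4 points |

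**The case against.** The strongest reply is that nothing here is an error. In a randomised trial the unadjusted test is valid, the total was computed for exactly that test, and it delivers the promised 80%. The covariate list is formally open, and an analysis plan that is not shown may complete it. Baseline is also not wholly ignored: the responder indicator, a halving of crying time, uses it, and the random effects models of trends may do so. Feeding is already handled through stratification and a planned subgroup analysis.

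Most of this stands, and it limits the point to efficiency. It does not remove it. The responder indicator and the trend models are additional analyses and do not sharpen the day-28 comparison. An open list that names weaker factors and only one of two stratifiers is still the method as published.

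A reader might go further in three ways, and the document does not support them:

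- **That the type I error is inflated** because t, rank and adjusted tests are all mentioned. This would require that the most favourable p-value be reported, and nothing says so. The section ties its summaries to the shape of the distribution and anticipates skew, and the choice of deciding test may be settled in the analysis plan. A baseline-adjusted test cannot be counted among the candidates, since the plan does not list one.
- **That the estimate is biased** by chance imbalance in baseline crying. Such imbalance is sampling variation, already reflected in the unadjusted confidence interval.
- **That a third more infants are gained.** That is the r = 0.5 case (171 against 128), the top of an assumed range.

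**Conclusion.** The point holds as a loss of precision and is a free improvement, not a defect that must be repaired before the trial can be relied on. The unadjusted test is valid and 160 infants is not wrong. Baseline adjustment would raise power from 80.1% to between about 80.5% (r = 0.1) and 90.0% (r = 0.5). The direction is sure for any meaningful correlation; the size is not, because r is an assumption, and values of 0.3 or below are plausible in this population. Nearly all the gain comes from baseline crying/fussing time. The case for feeding is that the analysis should match the stratified randomisation, with a gain of about 0.4 to 2.4 points if the strata differ by 0.2 to 0.5 SD.

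**What to change.** Before unblinding, name as the primary analysis a linear model of day-28 crying/fussing time (minutes per 24 hours) on treatment, baseline crying/fussing time, feeding stratum and age stratum. Report the adjusted mean difference with its 95% confidence interval, using robust or bootstrap standard errors if the data are skewed. This also keeps the analysis on the scale of the sample size statement, a "minimum effect size of 0.5 standard deviations, difference in the mean daily crying time between treatment groups".

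In the secondary models, include both strata and the outcome's own baseline value where it was collected; Table 1 shows none for the infant functioning score. Keep the t test, the rank test and the longer covariate list as sensitivity analyses.

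The cost is a change of analysis wording. Every variable is already collected, and neither the sample size nor any study procedure changes.

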## Discussion

Infant colic is common, distressing, impacts adversely on maternal mental health, and is a risk factor for shaken baby syndrome. An effective, practical and acceptable intervention for infant colic would represent a major clinical and public health advance. As our trial will include breast *and* formula-fed babies, regardless of maternal diet, our results can be generalised to most babies presenting with colic. If cost-effective, the simplicity of the intervention is such that it could be widely taken up as a new standard of care in the primary and secondary care sectors.

With the boom of probiotic products appearing on the market, the use of probiotics in the community is becoming more widespread. It is therefore important to provide sufficient sound scientific evidence for its effectiveness in infant colic before it becomes incorporated into regular use by the community, and avoid unnecessary consumption of costly products if the intervention is not found to be effective.

## Abbreviations

*L reuteri*: *Lactobacillus reuteri*; *E coli*: *Eschericia coli*; RCH: Royal Children’s Hospital; ED: Emergency Department; CEBU: Clinical Epidemiology and Biostatistics Unit; cfu: Colony forming units; SMS: Short message service; mins: Minutes; ml: Milliliter; kg: Kilogram; mg: Milligram.
